### Primary and secondary outcomes

Primary outcome is the one-year pre- to post-implementation change in HbA1c.

Secondary outcomes are the one-year differences in cholesterol levels and systolic and diastolic blood pressure. A composite patient score and a composite process score are calculated representing the change in diabetes (process) control and associated cardiovascular risk [19]. The composite patient score consists of reaching the evidence-based targets for glycated hemoglobin, blood pressure (systolic and diastolic), and cholesterol. The process composite score consists of meeting the evidence-based targets of the number of blood pressure measurements, the number of laboratory results of HbA1c, cholesterol and micro-albuminuria, a prescription of statin (yes/no), if high cardiovascular risk a prescription of aspirin/clopidogrel (yes/no), if hypertension or nephropathy ACE inhibition/sartan (yes/no).

Outcomes that cannot be reliably detected from the electronic medical records such as smoking status, and feet and eye examinations are excluded from the composite scores, as well as outcomes in which family physicians’ influences are minimal (*e*.*g*., BMI, physical activity, etc.).

Outcomes of the composite scores with their respective targets are shown in Table 1. Recommendations and targets are based on the diabetes guidelines of Domus Medica [20] and the Belgian ‘Zorgtraject diabetes’ [21].

**Table 1 T1:** Variables included in the composite scores

***Variable***	***Process target***	***Maximum score per period****	***Clinical target***	***Maximum score per period***^**†**^
HbA1c	Quarterly	2	< 7%	1
Blood pressure	Quarterly	2	< 130/80 mm Hg	1
Cholesterol (LDL, HDL, Total)	Annual	1	LDL < 100 mg/dL	1
Microalbuminuria check	Annual	1		
A prescription of statin	Yes/no	1		
If high cardiovascular risk, a prescription of aspirin/clopidogrel	Yes/no	1		
If hypertension or nephropathy, ACE inhibition/sartan	Yes/no	1		
Total		9		3

*Maximum score for process composite per period = 9 (7 variables).

^†^ Maximum score for patient composite per period = 3 (3 variables).

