Each of the parameters in the composite scores is compared with their respective target. Each outcome that meets the target will be assigned one point. If all outcomes meet the targets, a maximum score of 3 points will be assigned to the patient composite score and a maximum score of 9 points will be assigned to the process composite score. If we cannot find any data about the process variable, we will assume that it did not happen. A variable that improves during the intervention period will be scored as +1; each variable that worsens will be scored as −1; and each variable that does not change will be scored as 0. As such, composite scores can be grouped into three categories: worsened, unchanged or improved.

The follow-up period will be 12 months. Outcomes will be collected at five points: before the start of the study, at 3 months, at 6 months, at 9 months and at 12 months, with the differences between pre- and post-implementation forming the outcome scores. A mean will be calculated for the intervention and control groups. The trial will be terminated at one of the interim analysis points when a mean difference of 0.3% might be reached for the primary outcome of HbA1c change.

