### Sample size

Based on the data in the literature, a mean difference of 0.3% in HbA1c change could be considered clinically significant (SD of HbA1c change 1.3%) [23-25]. To detect a mean difference of 0.3% in HbA1c change at four post-treatment occasions, with a two-sided unpaired *t*-test, a 5% family-wise significance level and Bonferroni correction for multiple testing, 1:1 allocation and a power of 80%, a sample size of 463 patients in each group will be necessary, assuming a withdrawal rate of 10%. Additional adjustment for clustering of patients within physician practices by the design effect [26], assuming 10 patients per cluster and an intra-class correlation coefficient of 0.047 based on data in the literature [27], leads to a sample size of 659 patients in each arm. Sample size calculations were based on historical data. They can be adjusted after baseline registrations if correct standard deviations and intra-cluster correlation coefficients are known. Sample size calculation was performed using SAS software.

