### Data analysis

Descriptive statistics will be provided regarding baseline variables of the patients and the family physicians. Intervention and control groups will be compared regarding baseline variables to evaluate the randomization. Linear mixed models will be used for continuous patient-level variables, with a random intercept to account for clustering of patients within physician practices. Logistic regression models based on generalized estimating equations (GEE) to account for clustering will be used for binary patient-level variables.

Differences between intervention and control groups regarding continuous outcome measures (change versus baseline in HbA1c, cholesterol levels, and blood pressure) will be assessed using linear mixed models (multilevel regression models) with random intercepts for physician practices and random intercepts for patients to account for repeated measurements over time. The primary fixed effect of interest will be the difference between intervention and control group, which will be tested at each time point (3 m, 6 m, 9 m and 12 m). If important differences in baseline characteristics are demonstrated between both groups, we will account for that by including the relevant variables in the model.

Differences between intervention and control groups regarding three-level composite scores (worsening, unchanged, improvement) will be assessed using random-effects proportional odds models, or, in case the proportional odds assumptions do not hold, baseline-category logits models, with random intercepts for physician practices and random intercepts for patients to account for repeated measurements over time. As with the analysis of continuous outcomes, differences between intervention and control groups will be tested at all time-points, and correction for imbalance in baseline characteristics will be applied if indicated.

To study the effect of the actual use of the EBMeDS system on the outcome measures, models similar to those described above will be used for analyzing the effect of intervention. However, they will now include a measure for the use of EBMeDS as the main explanatory variable, and will restrict analysis to the data obtained in the intervention group.

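### The outcome data choose the model for the two secondary composite scores, so the arm comparison can change from one ordered contrast to two unordered ones

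*Protocol article*

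**What the plan says.** Under Primary and secondary outcomes, HbA1c is primary: "Primary outcome is the one-year pre- to post-implementation change in HbA1c". The composites are introduced among the secondary outcomes: "A composite patient score and a composite process score are calculated". Their scale is ordered by construction, because variables are scored +1, 0 or −1 for getting better, staying the same or getting worse, so that "composite scores can be grouped into three categories: worsened, unchanged or improved".

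Under Data analysis, these three-level scores are to be modelled by "random-effects proportional odds models, or, in case the proportional odds assumptions do not hold, baseline-category logits models", with random intercepts for practices and for patients. For the composites, as for the continuous outcomes, "differences between intervention and control groups will be tested at all time-points".

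The only significance level in the article is in Sample size, for HbA1c: "a 5% family-wise significance level and Bonferroni correction for multiple testing". None is given for the composites.

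**The concern.** Which model is used, and so which arm contrast is tested, depends on the outcome data. Under proportional odds the arm effect at a time point is a single odds ratio for a shift towards improvement. Under baseline-category logits it is two log odds ratios (for example worsened against unchanged and improved against unchanged), and the model does not use the order of the categories. An arm could then show both more improved and more worsened patients, and the composite would have no single direction. That holds at any significance level and whatever triggers the switch.

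The switch can also be related to the result. If the intervention has no effect, every arm odds ratio is 1 and proportional odds holds exactly for the arm term. A formal check of that term then fails only when the arms' category distributions happen to differ, which is when a test based on the fallback model tends to reject.

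**Working it through.** **The plan's own figures.** The article gives no error rate or sample size for the composites. Its HbA1c figures do reproduce. With a difference of 0.3, an SD of 1.3, a two-sided level of 0.05/4 = 0.0125 and 80% power, the t-test needs 421 per arm. Then 421 × 1.1 = 463.1 (stated 463). The design effect is 1 + 9 × 0.047 = 1.423, and 463 × 1.423 = 658.8 (stated 659). So the 5% level is split over four occasions for HbA1c. Nothing equivalent is stated for the composites, and 5% per test is assumed below.

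**Set-up.** Take two arms, three ordered categories, one time point and no treatment effect. The two-degree-of-freedom likelihood-ratio statistic for any arm difference is the sum of two parts:
- T², the one-degree-of-freedom proportional odds arm statistic;
- D², the one-degree-of-freedom statistic for departure from proportionality.

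In large samples under the null these are independent chi-squares. Let c be the level of the proportionality check. The rule is: if D² does not reject at level c, test T² against 3.841; otherwise test T² + D² against 5.991. Then

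false-positive rate = (1 − c) × 0.05 + c × P(T² + D² > 5.991 given that D² rejects).

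| Check level c | P(reject given switch) | Rate |
|---|---|---|
| 1% | 1.000 | 0.99 × 0.05 + 0.01 × 1.000 = 0.0595 |
| 5% | 0.498 | 0.95 × 0.05 + 0.05 × 0.498 = 0.0724 |
| 10% | 0.297 | 0.90 × 0.05 + 0.10 × 0.297 = 0.0747 |

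At c = 1% the conditional probability is 1 because the check's critical value, 6.635, already exceeds 5.991. If the per-test level were 0.0125 instead, c = 5% gives 0.95 × 0.0125 + 0.05 × 0.147 = 0.0192. One four-degree-of-freedom check over all time points at 5% gives about 6.0% per time point.

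**Simulation.** I used 421 independent patients per arm, 200,000 trials per scenario and four null category distributions, from 10/70/20 to 25/25/50 (worsened/unchanged/improved, %). With a 5% check:
- proportional odds always: 4.9% to 5.1%;
- baseline-category logits always, joint test: 4.9% to 5.1%;
- two-stage rule, joint fallback: 7.2% to 7.3%;
- two-stage rule, either contrast with Bonferroni adjustment: 7.1% to 8.0%;
- two-stage rule, either contrast unadjusted: 7.3% to 9.3%, depending on the reference category.

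Each model used alone with one test keeps 5%. The excess comes from the switch.

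**Power.** Assume a true common odds ratio of 1.45 from categories 0.25/0.40/0.35, with 659 × 0.9 = 593 patients per arm and 593/1.423 = 417 effective. This borrows the sample-size section's intra-class correlation for a different outcome. Simulated power is 82.5% with proportional odds always and 74.4% with the joint baseline-category test always. Under the two-stage rule with a 5% check the switch occurs only about 5% of the time, and power is 0.95 × 0.825 + 0.05 × 0.970 = 0.832.

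**The case against.** Naming a fallback in advance is a recognised way to handle a failed assumption. The criterion for failure, and whether the fallback is judged jointly or by separate contrasts, are details that an article may leave to the full protocol or analysis plan. Their absence is not held against the plan here. What remains is the published switch itself, which a written criterion would not remove.

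A reader might draw four stronger conclusions, and the document supports none of them.

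- **That the rule necessarily pushes the error rate above 5%.** The article does not say that proportionality is tested formally, or on the arm term. If time or covariate terms alone drive the switch, a joint test keeps 5%. The 5% level is itself assumed for these outcomes.
- **That the rate is about 9%.** This needs either of two unadjusted contrasts to count as a positive result. The article does not say so, and a joint test fits its wording equally well.
- **That the rule costs some nine points of power (83% to 74%).** That compares one model always with the other always. Where odds are truly proportional, the two-stage rule keeps about 83%. The loss arises only when the fallback is used for reasons unrelated to treatment.
- **That the trial's main result is at risk.** HbA1c is analysed by linear mixed models and is untouched.

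Two further points stand. The calculations use independent patients in a single two-by-three table, whereas the planned models have practice and patient random effects, so the size of the excess there is indicative. Opposite movements in worsened and improved are also a real finding that a single odds ratio could hide, so the separate estimates must be shown. Analyst blinding does not help, because two-sided tests do not depend on the arm labels.

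**Conclusion.** The point holds in a limited form. The plan lets the outcome data choose between one ordered arm contrast and two unordered ones, for scores it defines as ordered. Loss of a single direction for the composite is possible whenever the fallback is used.

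The error-rate effect is conditional. With a formal check involving the arm term and an assumed 5% level, each test runs at about 6% to 7.5% with a joint fallback. If either unadjusted contrast counts, it reaches up to 9.3% with a 5% check and 10.6% with a 10% check. With a check that does not involve the arm, the joint test keeps 5% and the cost is power.

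Only the two secondary composites are affected. For scale, testing one composite at four time points at an unadjusted 5% would by itself give a family-wise rate of 11.4% to 18.5% (between-time correlation 0.8 to 0). That is a separate and larger matter.

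**What to change.** State in the analysis section that, at each time point tested, the common odds ratio from the random-effects proportional odds model is the deciding arm contrast for each composite, whatever the proportionality check shows. Its arm test is valid under no treatment effect, where the arm term is proportional by definition. Report the baseline-category odds ratios, or the two separate cumulative odds ratios, beside it as a descriptive sensitivity analysis.

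The cost is one or two sentences and no extra data. The downside is small: when proportionality fails, the common odds ratio is an average shift and must be read with the category-specific estimates. The choice of time points need not change for this fix.

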### Process evaluation

In the process evaluation, actual use of the system as well as users’ perceptions about the feasibility of the electronic decision support will be measured. These aspects are two necessary components of a process evaluation [22].

Scripts are automatically triggered, and users can see that a script is available from their main screen but have to click to view the script content. As such, click events can give us an indication of physicians’ interest in using the system. A new record is inserted in the log file for each script that is triggered. The following data of actual use are collected in a log file at the physician level: identification code of the script; type of script that is triggered and opened (Reminder, Interaction, Contra-indication, Drugs to avoid, Indication, GuideLine Link); script node expanded (yes/no): *e*.*g*., a long reminder displays when a short reminder is clicked; request for the script information (yes/no).

As such, the percentage and the type of scripts that were opened will be calculated, as well as the percentage of scripts that were expanded and the percentage of scripts for which the script information was requested.

Process information regarding actual use of the Evidence Linker will be logged in a similar way.

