### Data collection

Data will be automatically extracted from the EMR of the family physician for all patients who satisfy the eligibility criteria. Data will be extracted at five points in time: before the start of the study, at 3 months, at 6 months, at 9 months, and at 12 months. All outcomes can be reliably determined from the electronic medical records. When a physician closes HealthOne, a reminder will be shown to export the data. The family physician can visualize the data and has to confirm if he agrees to export. Modifications to this file cannot be made by the physician.

Identification data of the patient will be manually converted to an output code via a hashing program installed on the computer of the family physician. Data will be sent by mail to an independent third person. This person will be responsible for uncoupling the identifiable data of the family physician (name and e-mail address) from the patient data and the data related to the actual use of the system. A meaningless code will be allocated to the physician’s data and its corresponding patient and use data. The coupling between these data will be exclusively possessed by this person and will be used to couple the data at the different points in time.

These coded data will be sent securely to the researcher. Patient data will be sent to the researcher at the five interim analysis points. Data concerning EBMeDS use will be sent once to the researcher at the end of the study period after patient data are analyzed. Data related to system use will be used to explore possible relationships between the patient outcomes and the actual use of the system. As there is only one file of actual use for the physicians in the intervention group, the researcher would not be blinded if these data were sent together with the patient data.

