### Ethics

Before the start of study, we will present the physicians with an informed consent that outlines the EBMeDS intervention and the purpose of the trial to study the effectiveness of the system.

Individual informed consent from the patient cannot be sought. Reminders show up unexpectedly during practice when patient data deviate from evidence-based targets. It is not practical to ask for informed consent at these moments. Furthermore, reminding the physician of the informed consent forms at every consultation may bias the study results in favor of the intervention.

Data exports will be compliant with privacy legislation. Registration of the data processing to notify the Belgian Privacy Commission was performed on the commission website: http://www.privacycommission.be. Authorization for the use of medical and personal data was requested from the Sector Committee of Health.

Ethics committee approval for this study was obtained from the University Hospitals Leuven Medical Ethics Committee in May 2013.

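### The within-arm analysis of EBMeDS use is worded as an effect, but physician motivation confounds it and no planned adjustment can act on it

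*Protocol article*

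**What the plan says.** The last paragraph of Data analysis states its aim as "To study the effect of the actual use of the EBMeDS system on the outcome measures". The models follow those for the randomised comparison, whose continuous outcomes are changes from baseline. Of these models the section says that "they will now include a measure for the use of EBMeDS as the main explanatory variable, and will restrict analysis to the data obtained in" one arm, the one given EBMeDS. The use measure is not defined there. The covariate rule earlier in the section adds baseline variables only when the intervention and control groups differ importantly.

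Three other sections bear on this:

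- **Process evaluation.** Scripts fire automatically, but "users can see that a script is available from their main screen but have to click to view the script content". The authors add that "click events can give us an indication of physicians’ interest in using the system". Use is logged per physician. The summaries named are the percentage and type of scripts opened, the percentage expanded and the percentage with information requested. No count is named.
- **Ethics.** "Reminders show up unexpectedly during practice when patient data deviate from evidence-based targets".
- **Data collection.** The same analysis is put more modestly: "Data related to system use will be used to explore possible relationships between the patient outcomes and the actual use of the system". The use file reaches the researcher only after the patient data have been analysed.

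**The concern.** Randomisation supports the comparison of intervention with control practices. It gives no support to a comparison of heavier with lighter users inside the intervention arm. Opening a script is the physician's choice, so physicians who open more may also manage diabetes more actively in ways that owe nothing to EBMeDS. Any measure based on opening carries that difference, and the stated covariate rule has nothing to compare within one arm.

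A second route is conditional. If the measure counted triggered or opened diabetes scripts, it would rise with off-target baseline values, and these tend to fall on re-measurement anyway.

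This is the only planned analysis that links amount of use to patient outcome, and the Discussion expects the results to apply nationally. A spurious gradient, reported as an effect, could be used to explain away a null randomised result on the ground that the system works when it is used.

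**Working it through.** **Inputs from the protocol (Sample size).** Difference 0.3%, SD of HbA1c change 1.3%, ICC 0.047, 10 patients per practice, four tests at 0.05/4 = 0.0125, power 80%, withdrawal 10%. The plan states no figure for the use analysis. Its sample size reproduces: the two-sided t-test needs 421 per arm; 421 × 1.10 = 463; the design effect is 1 + 9 × 0.047 = 1.423; 463 × 1.423 = 659. That is 659/10 ≈ 66 practices per arm.

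**Assumptions not in the protocol.** Mean baseline HbA1c 7.2%; level SD 1.1, 1.3 or 1.5; three times as many scripts triggered at HbA1c of 7% or above; one physician per practice; more motivated physicians open more scripts. Each setting was run 150 times on 66 practices of 10 patients, with GEE clustered on practice and no effect of use.

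**Step 1: motivation.** Suppose a physician one SD more motivated lowers HbA1c by 0.1 or 0.2 points by means other than EBMeDS. For plausibility, if the ICC applies to change, the between-practice variance is 0.047 × 1.3² = 0.079 (SD 0.28). The assumed effects then take up 0.01/0.079 = 13% or 0.04/0.079 = 50% of it.

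| Motivation effect per SD | Slope per SD of percentage opened | p < 0.05 | Slope with baseline HbA1c added | p < 0.05 |
|---|---|---|---|---|
| 0.1 | about −0.09 | 39–44% | −0.08 to −0.09 | 45–48% |
| 0.2 | −0.16 to −0.18 | 87–91% | −0.17 to −0.18 | 93% |

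The simulated practice effect is common to baseline and follow-up, so it cancels from change and these rejection rates are somewhat high. A hand check with the plan's design effect gives the slope a standard error of √(1.423 × 1.69/660) = 0.060. A slope of −0.09 then gives z = 1.49 and rejection in about 32% of trials; −0.17 gives z = 2.82 and about 80%. The size of the spurious slope does not change.

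**Step 2: regression to the mean.** With equal SD s at both times, 1.3² = 2s²(1 − ρ), so 1 − ρ = 1.69/(2s²). This is 0.70, 0.50 and 0.38 for s = 1.1, 1.3 and 1.5. A patient who starts 1 point above the mean is expected to fall by that amount with no intervention. Whether this reaches the use slope depends on the measure (no effect of use, no motivation effect):

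| Use measure | Slope per SD | p < 0.05 |
|---|---|---|
| Triggered scripts, count per patient | −0.26 to −0.34 | 99.5–100% (reported as 100%) |
| Opened scripts, count per patient | −0.16 to −0.22 | 91–100% |
| Opened scripts, count per physician | about −0.04 | 13–19% |
| Percentage opened, per physician | about 0 | 8–11% |
| Triggered count per patient, baseline HbA1c added | about 0 | 7–9% |

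For percentage opened there is no bias. The 8–11% mainly reflects robust standard errors with 66 clusters and few runs (Monte Carlo standard error √(0.05 × 0.95/150) = 1.8 points); a separate simulation of 2,000 trials gave 5%.

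**Step 3: what adjustment does.** Baseline HbA1c removes the regression-to-the-mean strand (Step 2, last row) and leaves the motivation strand untouched (Step 1).

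**The case against.** The strongest reply is that this is an exploratory analysis, described as such under Data collection; that confounding by motivation is a familiar limit of any within-arm use analysis; and that the exact use variable and covariates belong in a fuller document that is not shown. Much of this stands. An article need not list every covariate, and the randomised contrast is already planned in both arms. But the article does fix the restriction to one arm, the word effect, and a covariate rule that cannot operate there. Its two descriptions of the analysis also differ in strength.

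A reader might infer something stronger: that regression to the mean will almost certainly produce a false dose-response close to the 0.3% the trial calls clinically significant. The documents do not support that. In a worst case, where each patient at or above 7% triggers exactly one script and nothing else is counted, practice tertiles of triggered scripts differ by −0.27% and 85% of null trials are significant. That requires a diabetes-only count. Process evaluation names only percentages, for which the same simulation gives 0.00% and 5%. Reminders also cover all clinical areas: with an assumed three unrelated scripts per patient, rejection for triggered counts fell to 9–14%. A count is not formally excluded, because Data analysis leaves the measure open, but none is planned.

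Nor is the restriction to one arm an error in itself. Control practices have no EBMeDS use, so adding them cannot show whether more use brings more benefit.

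**Conclusion.** The point holds as one of confounding and wording in a secondary analysis. As written, the use–outcome slope has no randomised support for being called an effect, and physician motivation biases every opening-based measure. The bias is about −0.09 HbA1c points per SD of percentage opened if motivation is worth 0.1 points per SD, and −0.16 to −0.18 if it is worth 0.2. Both motivation effects are assumptions, since the protocol gives none, and the figures are illustrative. Regression to the mean matters only for counts of triggered or opened diabetes scripts. A reader might also infer that the trial's main result is compromised; it is not, as the primary comparison, the sample size and the error control do not use this analysis.

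**What to change.** In the last paragraph of Data analysis:

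1. Define the use measure as the physician-level percentage of triggered scripts that were opened, with a reference to Process evaluation. Fix this before the use file is released, because by then the patient outcomes will have been analysed.
2. Always include the baseline value of the outcome and the physician's age, gender and years of experience, which Baseline measurements already lists. These covariates will capture motivation only in part, so item 3 is still needed.
3. Replace effect with association, in line with Data collection, and state that the result cannot be read as a causal dose-response or used to explain a null randomised result.

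The cost is a few sentences and some model terms, with no new data items.

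Optionally, add a secondary complier-average estimate from both arms, with practice allocation as the instrument, control-arm use set to zero and standard errors clustered on practice. In essence it divides the randomised difference by mean use in the intervention arm, so it rescales the planned contrast and does not describe a within-arm gradient. Its interval is wider, and it assumes that allocation acts only through use; scripts displayed but not opened may breach that assumption.
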